## Abstract

**Background:**

There are no therapies proven to diminish the muscle wasting that occurs in patients after major trauma who are admitted to the intensive care unit (ICU). β-Hydroxy-β-methylbutyrate (HMB) is a nutrition intervention that may attenuate muscle loss and, thereby, improve recovery. The primary aim of this study is to determine the feasibility of a blinded randomised clinical trial of HMB supplementation to patients after major trauma who are admitted to the ICU. Secondary aims are to establish estimates for the impact of HMB when compared to placebo on muscle mass and nutrition-related patient outcomes.

**Methods:**

This prospective, single-centre, blinded, randomised, placebo-controlled, parallel-group, feasibility trial with allocation concealment will recruit 50 participants over 18 months. After informed consent, participants will be randomised [1:1] to receive either the intervention (three grams of HMB dissolved in either 150 ml of orange juice for those allowed oral intake or 150 ml of water for those being enterally fed) or placebo (150 ml of orange juice for those allowed oral intake or 150 ml of water for those being enterally fed). The intervention will be commenced in ICU, continued after ICU discharge and ceased at hospital discharge or day 28 post randomisation, whichever occurs first. The primary outcome is the feasibility of administering the intervention. Secondary outcomes include change in muscle thickness using ultrasound and other nutritional and patient-centred outcomes.

**Discussion:**

This study aims to determine the feasibility of administering HMB to critically ill multi-trauma patients throughout ICU admission until hospital discharge. Results will inform design of a larger randomised clinical trial.

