## Background

Patients admitted to the intensive care unit (ICU) after a traumatic injury frequently suffer from a rapid reduction in muscle mass leading to substantial muscle weakness [1–4]. These changes in body composition and muscle strength are associated with prolonged hospital length of stay (LOS), increased mortality after ICU discharge, reductions in post-hospital discharge functional recovery and diminished quality of life (QOL) [1–5].

Various interventions have been evaluated in attempts to attenuate muscle loss in critically ill patients. These include nutritional interventions, such as increasing calorie [6, 7] and/or protein provision [6–9], providing amino acid supplementation [10, 11], enteral immunonutrition [12], physical interventions such as resistance exercise and/or early mobilisation [13, 14] and drugs, such as anabolic steroids [15]. However, the effects have been inconsistent [16–18]. This may be because the interventions chosen are truly of no benefit. Alternatively, the lack of effect may be due to the period of study. The majority of trials evaluating the impact of nutrition interventions in the critically ill are limited to the ICU admission [19]. Accordingly, the nutritional intervention is administered only for a short duration and during a period when enteral absorption of nutrients is most impaired. It is, therefore, biologically plausible that the provision of a nutrition intervention over an increased duration is more likely to attenuate muscle loss and improve functional outcomes when recovering from critical illness [20].

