Hitherto, only three randomised clinical trials have evaluated the effect of HMB supplementation in critically ill populations [29–31]. All three trials limited the period of intervention to the ICU admission. In a single centre trial of 100 severely ill trauma patients, Kuhls and colleagues reported that 3 g/day of HMB, when compared to placebo, markedly attenuated negative nitrogen balance [29]. Hsieh and colleagues examined the impact of HMB on inflammatory markers in critically ill chronic obstructive pulmonary disease (COPD) patients. They reported white blood cell count, C-reactive protein and creatinine to be significantly lower, whilst cholesterol and total protein were significantly higher after HMB supplementation [30]. However, neither study investigated the effect of HMB on muscle mass or physical function. Nakamura and colleagues [2] evaluated the impact of HMB in conjunction with arginine and glutamine when compared to control (no HMB supplementation) on change in muscle volume using computed tomography during the ICU admission in 88 severely ill medical or surgical patients [31]. Both groups were observed to lose muscle volume over the acute 10-day study period with point estimate favouring a greater volume of femoral muscle retained in those receiving HMB [31].

To summarise, it is not known whether nutritional HMB supplementation will attenuate muscle loss and improve outcomes in patients recovering from major trauma. It is also unclear if it is feasible to conduct a trial of a blinded nutrition intervention in the ICU and continue after ICU discharge, whilst collecting adequate outcome data.

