### Trial intervention and control

The trial intervention is β-hydroxy-β-methylbutyrate (HMB). HMB has been purchased from Myprotein (Warrington, UK). Three grams of HMB is dissolved in 150 ml of fluid. To ensure blinding of participants is maintained, orange juice is the fluid for those allowed oral intake and water for those being enterally fed. Orange juice completely masks the taste and smell of the HMB supplement. HMB powder dissolves completely in water and does not impact the viscosity of the solution. The control is 150 ml of orange juice for those allowed oral intake, or 150 ml of water for those being enterally fed. If a patient is restricted to ingesting only thickened fluids and unable to receive the intervention/control via an enteral feeding tube, Flavour Creations™ orange juice thickened to the appropriate viscosity will be used to blind the intervention/control.

Patients will receive the intervention or control from day 1 post enrolment until hospital discharge or study day 28, whichever occurs first. If a patient is readmitted to hospital within 28 days from randomisation, study procedures and administration of the intervention or control will resume. The intervention or control will be documented in the electronic medication record by the treating team and administered by the nurse caring for the patient. The number of doses prescribed and consumed will be recorded for the duration of the study. The nurse caring for the patient will document patient compliance with the intervention or control and any tolerance issues voiced by the patient believed to be associated with the consumption of trial supplement. The reason for any missed doses will be recorded.

The investigator/s, patient, nurse and member of the treating team will be surveyed on day 1 post enrolment and then day 28 or hospital discharge, whichever occurs first, as to their blinding to the intervention/control as part of the feasibility criteria. All will be invited to take their best guess of whether the participant is receiving the intervention or placebo.

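### Adherence is reported as one percentage over the whole dosing period, although the question is whether HMB can be continued after ICU discharge; report the post-ICU part separately.

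*Protocol article*

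**What the plan says.** The article frames its question as continuation. The closing paragraph of the Abstract gives the aim as the "feasibility of administering HMB to critically ill multi-trauma patients throughout ICU admission until hospital discharge". The Background explains why this is new. In nutrition trials confined to the ICU, it says, "the nutritional intervention is administered only for a short duration". Of the three HMB trials in critically ill patients, it says "All three trials limited the period of intervention to the ICU admission". It then calls it unclear whether it is "feasible to conduct a trial of a blinded nutrition intervention in the ICU and continue after ICU discharge".

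Under Trial intervention and control, the dosing period is set: "Patients will receive the intervention or control from day 1 post enrolment until hospital discharge or study day 28, whichever occurs first". The same section states that "The number of doses prescribed and consumed will be recorded for the duration of the study", and that reasons for missed doses are noted. Table 2 lists administration as a daily item and also lists ICU length of stay.

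The Primary outcomes section defines adherence as the amount of HMB taken against the amount that full compliance would have given. The matching indicator is one percentage: the share of prescribed HMB doses that were taken. Neither statement separates the ICU from the later period, summarises doses per participant or names a target. The other indicators are the percentage of surveyed clinicians who identify the allocation correctly, the percentage of eligible patients recruited, and the percentage of enrolled patients retained to hospital discharge.

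**The concern.** The indicator does not isolate the part of the regimen that the question is about. Giving a supplement during the ICU stay is what the earlier trials already did; the open question is what happens afterwards. A percentage taken over all doses is a weighted average of the two phases. Its weight is the ICU share of doses, which the article does not give, so a reader of the single figure cannot recover the post-ICU result.

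The figure is also silent on quantity. Two participants can both be at 100%, one with almost no doses after ICU discharge and the other with several weeks of them.

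At stake is the design of the larger trial that these results are meant to inform. A reassuring overall figure could lead that trial to assume a post-ICU exposure that this study did not deliver.

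**Working it through.** There is no figure in the article to reproduce: it states no adherence target, expected adherence or dose split. The check therefore compares the indicator with the question, then shows by assumed inputs how far one figure can mislead.

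**Step 1. Does any other indicator measure post-ICU delivery?**
- Retention to hospital discharge counts patients, not doses. A retained participant may take few ward doses.
- The blinding surveys (day 1, then day 28 or discharge) measure guesses about allocation.
- Recruitment concerns entry to the trial.
- Reasons for missed doses are recorded, but no listed indicator uses them.

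The adherence percentage is the only indicator of delivery.

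**Step 2. What can the single percentage hide?** Let *w* be the ICU share of prescribed doses, *A*(ICU) and *A*(post) the adherence in each phase, and *P* the overall percentage.

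*P* = *w* × *A*(ICU) + (1 − *w*) × *A*(post), so *A*(post) = [*P* − *w* × *A*(ICU)] / (1 − *w*)

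Assumed: *P* = 0.80 and *A*(ICU) = 0.95.

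| ICU share *w* | Calculation | Post-ICU adherence |
|---|---|---|
| 30% | (0.80 − 0.285) / 0.70 | 74% |
| 50% | (0.80 − 0.475) / 0.50 | 65% |
| 70% | (0.80 − 0.665) / 0.30 | 45% |

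**Step 3. The same check in the other direction.** Assumed: *A*(ICU) = 0.95 and *A*(post) = 0.50.

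| ICU share *w* | Calculation | Overall percentage |
|---|---|---|
| 30% | 0.285 + 0.350 | 63.5% |
| 50% | 0.475 + 0.250 | 72.5% |
| 70% | 0.665 + 0.150 | 81.5% |
| 80% | 0.760 + 0.100 | 86.0% |

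Masking is strong when ICU doses dominate. When most doses fall after the ICU, a poor post-ICU phase largely shows in the overall figure. Reported separately, the results read 95% and 50% in every row.

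**Step 4. Quantity delivered.** Dosing ends at hospital discharge or day 28, so the denominator follows the stay. With one dose a day (assumed from the daily schedule in Table 2), 6 of 6 and 28 of 28 doses both give 100%. Neither value shows how many of those doses came after ICU discharge.

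**Step 5. Do the recorded data support a split?** Administration is recorded daily, ICU length of stay is collected, and Table 2 schedules physical function assessments at ICU discharge. Each dose day can therefore be placed in or after the ICU. Route of administration is not listed as recorded, although the fluid used differs between oral and enteral patients.

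**The case against.** The strongest objection is that tabulating a named indicator by location is descriptive detail that a journal article leaves to the full protocol or the statistical analysis plan, neither of which is shown. Nothing in the article forbids a split, and *pooled* is a reading of an undivided percentage, not the article's word. This stands in part: it makes the point a low-cost improvement, not an error. It does not remove the mismatch, because the article itself states which primary feasibility indicators will be reported.

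The Background sentence on the unknown also goes on to collection of adequate outcome data, and the Study objectives list blinding, recruitment and retention, outcome measurement and competing mortality. Post-ICU feasibility therefore does not rest on adherence alone. That is correct, but none of those measures delivery of the supplement.

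Three stronger readings are tempting, and the article does not support them:
- *A failed ward phase could pass as feasible.* There is no pass mark; the indicators are only to be reported.
- *Scoring 6 of 6 doses as 100% is wrong.* A participant discharged after six days who took every dose received the full intended regimen. The percentage is right as adherence; it does not measure exposure. Length of stay is reported by group and unequal duration is named as a limitation in the Discussion, so short stays would not be invisible.
- *ICU doses go by tube and ward doses are drunk.* The article states no such pattern and says that the nurse caring for the patient administers the supplement.

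Finally, enrolment follows two full calendar days in the ICU and may come later, so early ICU days contribute no doses. This lowers the ICU share and weakens the masking by an unknown amount.

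**Conclusion.** The point holds as a mismatch between question and indicator. The question is continuation after ICU discharge; the only delivery indicator is one percentage that does not isolate that phase or show how much was given in it.

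The possible size is 74% to 45% post-ICU adherence behind the same overall 80%. This rests on assumed ICU adherence of 95% and assumed ICU dose shares of 30% to 70%; none of these comes from the article. If post-ICU doses dominate, the masking is modest. The lack of information on post-ICU quantity does not depend on the dose mix.

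The consequence is a possibly misleading feasibility conclusion carried into the design of the larger trial. It does not make the study invalid, and no decision rule is affected.

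**What to change.** In the Primary outcomes section, replace the single adherence indicator by:
1. the percentage of prescribed HMB doses taken, separately for the ICU and the post-ICU period;
2. the number of doses taken per participant (median, IQR), in total and after ICU discharge, with the number of participants who contribute to the post-ICU figure.

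Base the statement about feasibility until hospital discharge on the post-ICU figures. State in advance to which period doses on the day of ICU discharge, and during any ICU readmission, are assigned. The overall percentage may stay as a summary line. A split by tube or oral route is optional, since recording of route is not stated and might need an added data item.

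The cost is the wording of one indicator and a few table rows. The daily administration record and ICU length of stay already support the main split. The price is precision: with 50 participants randomised 1:1, about 25 receive HMB, and the post-ICU figure rests on fewer doses and possibly fewer participants, so its interval will be wider.

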**Trial registration:**

The protocol is registered with Australian New Zealand Clinical Trials Registry (ANZCTR) ANZCTR: 12620001305910. UTN: U1111-1259-5534.

## Background

Patients admitted to the intensive care unit (ICU) after a traumatic injury frequently suffer from a rapid reduction in muscle mass leading to substantial muscle weakness [1–4]. These changes in body composition and muscle strength are associated with prolonged hospital length of stay (LOS), increased mortality after ICU discharge, reductions in post-hospital discharge functional recovery and diminished quality of life (QOL) [1–5].

Various interventions have been evaluated in attempts to attenuate muscle loss in critically ill patients. These include nutritional interventions, such as increasing calorie [6, 7] and/or protein provision [6–9], providing amino acid supplementation [10, 11], enteral immunonutrition [12], physical interventions such as resistance exercise and/or early mobilisation [13, 14] and drugs, such as anabolic steroids [15]. However, the effects have been inconsistent [16–18]. This may be because the interventions chosen are truly of no benefit. Alternatively, the lack of effect may be due to the period of study. The majority of trials evaluating the impact of nutrition interventions in the critically ill are limited to the ICU admission [19]. Accordingly, the nutritional intervention is administered only for a short duration and during a period when enteral absorption of nutrients is most impaired. It is, therefore, biologically plausible that the provision of a nutrition intervention over an increased duration is more likely to attenuate muscle loss and improve functional outcomes when recovering from critical illness [20].

β-Hydroxy-β-methylbutyrate (HMB) is a metabolite of the essential branched-chain amino acid leucine [21]. HMB has been studied across a variety of adult populations from healthy athletes to conditions of muscle wasting such as cachexia, acquired immunodeficiency syndrome (AIDS), cancer, chronic obstructive pulmonary disease and critical illness [22, 23]. It appears to be a promising inexpensive agent that has been shown to affect muscle protein turnover by suppressing proteolysis [24] and stimulating protein synthesis [25]. A dose of 3 g of HMB per day is associated with preservation of lean body mass in healthy older adults [26] and it appears to have no adverse health outcomes [27, 28]. In a blinded, randomised controlled trial of 19 healthy older adults, HMB administration attenuated the decline in lean body mass over 10 days of bed rest (HMB group lost an average of − 0.17 ± 0.19 kg total lean mass (*p* = 0.42, paired *t* test) versus control (− 2.05 ± 0.66 kg, *p* = 0.02, paired *t* test); *p* = 0.02, ANOVA) [26]. Given those with critical illness experience prolonged bed rest, HMB supplementation is a candidate nutritional intervention to attenuate muscle loss and weakness associated with critical illness.

Bear and colleagues conducted a systematic review and meta-analysis of randomised control trials that used HMB as a single agent or as part of a supplement [23]. When including a variety of cohorts, they reported that HMB administration improved muscle mass and strength [23], albeit all studies had high risk of bias and effect size was small.

Hitherto, only three randomised clinical trials have evaluated the effect of HMB supplementation in critically ill populations [29–31]. All three trials limited the period of intervention to the ICU admission. In a single centre trial of 100 severely ill trauma patients, Kuhls and colleagues reported that 3 g/day of HMB, when compared to placebo, markedly attenuated negative nitrogen balance [29]. Hsieh and colleagues examined the impact of HMB on inflammatory markers in critically ill chronic obstructive pulmonary disease (COPD) patients. They reported white blood cell count, C-reactive protein and creatinine to be significantly lower, whilst cholesterol and total protein were significantly higher after HMB supplementation [30]. However, neither study investigated the effect of HMB on muscle mass or physical function. Nakamura and colleagues [2] evaluated the impact of HMB in conjunction with arginine and glutamine when compared to control (no HMB supplementation) on change in muscle volume using computed tomography during the ICU admission in 88 severely ill medical or surgical patients [31]. Both groups were observed to lose muscle volume over the acute 10-day study period with point estimate favouring a greater volume of femoral muscle retained in those receiving HMB [31].

To summarise, it is not known whether nutritional HMB supplementation will attenuate muscle loss and improve outcomes in patients recovering from major trauma. It is also unclear if it is feasible to conduct a trial of a blinded nutrition intervention in the ICU and continue after ICU discharge, whilst collecting adequate outcome data.

### Study objectives

The objective is to determine the feasibility of undertaking a blinded randomised clinical trial of HMB supplementation to critically ill multi-trauma patients until day 28 post randomisation or hospital discharge. Feasibility will be established by evaluating:An ability to blind the intervention.The recruitment and retention rates according to the study methods.The ability to perform the outcomes measures within this patient cohort weekly until day 28 post randomisation or hospital discharge whichever occurs first and again at day 90 post enrolment.The extent to which mortality may be a competing risk in this patient cohort for nutritional and functional outcome assessments.

Secondary objectives are:To return initial estimates of effect size and variance associated with HMB treatment on muscle mass.To return initial estimates of effect size and variance associated with HMB treatment on other nutrition-related patient outcomes including changes in weight, nutritional status, nutrition intake, appetite, muscle strength, physical function and quality of life in a multi-trauma population compared to standard care.

## Methods/design

This will be a prospective, single-centre, placebo-controlled, two parallel-group, randomised feasibility trial with allocation concealment and blinded assessors. The design is in accordance with the Standard Protocol Items: Recommendations for Interventional Trials (SPIRIT 2013) [32] and the Consolidated Standards for Reporting of Trials CONSORT guidelines [33] (Fig. 1, modified consort). The study will be undertaken at the Royal Melbourne Hospital, which is a university-affiliated, trauma referral centre in Victoria treating up to 1000 patients per year with major trauma.

**Fig. 1 Fig1:**
[figure not shown]
Modified consort

### Study participants

Fifty participants who are admitted to the ICU due to traumatic injury will be recruited over an 18-month period (September 2020–February 2022). If participant recruitment is significantly less than this, the study can be extended for an additional 6–12 months. Patients will be screened following admission to ICU and identified as eligible according to the criteria presented in Table 1.

**Table 1 Tab1:** Inclusion and exclusion criteria

**Inclusion:** Adults, ≥ 18 years of age Completed two full calendar days in ICU The predominant reason for ICU admission was a traumatic injury Allowed enteral/ oral nutrition at the time of randomisation	
**Exclusion:** Death during ICU admission deemed to be inevitable Bilateral above knee amputation Patients assessed as requiring completely or predominantly parenteral nutrition Pregnancy Primary neuromuscular pathology present or strongly suspected this admission episode Presumed transection of the spinal cord at any level Medical decision treatment maker, participant or medical practitioner declined consent Limited research availability over enrolment timeframe Enrolment conflict with other research studies Unlikely to be able to participate in long term follow up measures Unable to obtain consent within 7 days from initial traumatic injury	

For study recruitment, consent will be sought from patients wherever they can give consent and it is practicable to approach them. Where it is not practicable to approach a person highly dependent on medical care, or the person is not capable of making such a decision, informed consent will be obtained from the person responsible as per local laws [34]. Consent to continue in the trial will be obtained from the participant if they recover adequately and they are deemed competent. The protocol and consent process has been approved by the Royal Melbourne Hospital Human Research Ethics Committee (2019.358). The protocol is registered with Australian New Zealand Clinical Trials Registry (ANZCTR 12620001305910).

